### Primary outcomes

The level of disability caused by migraine and the frequency, duration, and intensity of migraine attacks are the primary clinical outcomes, measured at baseline (prior to randomization), at the end of sessions 4 and 8 of the treatment, and at 3-month follow-up.

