### Specific aims

The specific aims and hypotheses for this pilot trial are (1) to examine, from baseline to 3 month follow-up, the level of disability due to migraine and the frequency, duration, and intensity of migraine attacks. We hypothesize that patients receiving WBT will show a better outcome compared to those assigned to the control condition (primary outcome); and (2) to examine, from baseline to 3 month follow-up, the level of anxiety, depression, psychological well-being, euthymia, and distress. We hypothesize that patients receiving WBT will show lower anxiety, depression, and distress, and greater psychological well-being compared to those assigned to the control condition (secondary outcome).

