#### Power calculation

The sample calculation was run via an a priori sample size calculator for Student’s *t* test. Cohen’s d was calculated on the basis of the results of (1) Mo’tamedi et al. [14], concerning the Migraine Disability Assessment scale score under acceptance and commitment therapy and under the control condition (this is the only study conducted in chronic migraine patients in which the Migraine Disability Assessment scale [38], which is one of our primary outcome measures, was used, although it tests the efficacy of a stress-oriented psychotherapeutic intervention which is different from WBT) and (2) Fava et al. [26], which tests the efficacy of WBT in a sample of patients with generalized anxiety disorder using, as the outcome measure, the Psychological Well-being scale [49], which is one of our secondary outcome measures. A Cohen’s d of 2.76 was obtained from Mo’tamedi et al. [14] and a Cohen’s d of 1.38 was obtained from Fava et al. [26]. Setting the power at 0.95 and the two-sided alpha at 0.05, a minimum sample size of 5 per group (two-tailed hypothesis) was obtained on the basis of Mo’tamedi et al. [14] and a minimum sample size of 15 per group (two-tailed hypothesis) was obtained on the basis of Fava et al. [26]. Thus, we will enroll 15 subjects per group for a total of 30 subjects. In case of drop-out, new enrolment will be run in order to have a final sample size of 15 subjects per group who complete the trial.

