## Discussion

The pharmacological treatment of chronic migraine has achieved remarkable progress in recent years [52, 53]. However, significant issues persist in patients who do not benefit from current drug treatments [54, 55] or for those with limited access to innovative approaches, such as anti-calcitonin gene-related peptide monoclonal antibodies, due to financial constraints. Current evidence on the efficacy of psychological interventions remains limited and unsatisfactory [8–18]. This study proposes a method aimed to empirically evaluate whether WBT provides a beneficial effect in chronic migraine patients. In particular, the present pilot study aims to test WBT versus a control condition as a psychological intervention for chronic migraine. The randomized trial represents a step towards the management of chronic migraine by means of psychological interventions.

We acknowledge some limitations of the study. Inclusion and exclusion criteria are proposed to maximize the safety of enrolled patients. However, such restrictions may reduce the possibility of generalization of results to the patient population with a more severe condition or those with high degrees of comorbidity. In addition, the sample size will not allow to test for potential differences in outcome between different durations of the chronic migraine or diverse levels of severity. Further, several key questions remain and could be the object for future studies, including whether, and at what size, differences in patient motivation or in the clinician–patient relationship may affect the outcomes. Should results of this pilot exploratory trial support our hypothesis, the next step will be a second trial enrolling a larger number of chronic migraine patients with a randomized and controlled multicentric design to investigate efficacy and potential mediators of treatment effects.

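### Four unranked primary outcomes share one hypothesis with no deciding comparison, so the 0.05 used for sizing is not tied to any test of it

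*Protocol article*

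**What the plan says.** Primary outcomes gives four measures equal standing: "The level of disability caused by migraine and the frequency, duration, and intensity of migraine attacks are the primary clinical outcomes". They are "measured at baseline (prior to randomization), at the end of sessions 4 and 8 of the treatment, and at 3-month follow-up", which makes three assessments after baseline.

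Specific aims states aim 1 as "to examine, from baseline to 3 month follow-up, the level of disability due to migraine and the frequency, duration, and intensity of migraine attacks" and ties all four to one directional statement: "We hypothesize that patients receiving WBT will show a better outcome compared to those assigned to the control condition (primary outcome". It does not say which measure or visit settles the matter, or whether one, several or all must favour WBT.

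Power calculation describes a calculation for one Student's t test: "The sample calculation was run via an a priori sample size calculator", and "Setting the power at 0.95 and the two-sided alpha at 0.05". Two effect sizes are used: d = 2.76 for the Migraine Disability Assessment score, which is a primary measure, and d = 1.38 for the Psychological Well-being scale, which is secondary. They give 5 and 15 per group, and the larger number is adopted.

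The Data analysis plan section says the focus is mainly descriptive. It then names ANCOVA for means and says means will be examined at all four time points. It names no key outcome or visit.

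The Discussion sets the consequence: "Should results of this pilot exploratory trial support our hypothesis, the next step will be a second trial".

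**The concern.** An error rate of 0.05 belongs to one identified comparison. Here the sizing assumes one comparison, the primary outcome list offers four, and the visit schedule multiplies these further. Because the document has no rule for when the hypothesis counts as supported, the rule could be settled after the data are seen.

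At stake is the meaning of a positive pilot. If WBT did nothing, a difference on one of four outcomes could still be presented as support and used to justify a larger trial. A reader could not tell whether that outcome was the intended one or the one that happened to differ. Which outcome decides a primary hypothesis is a protocol choice, and this document makes that choice by listing four without ranking them.

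**Working it through.** **Inputs.** Four primary outcomes and three post-baseline visits (Primary outcomes); one directional hypothesis (Specific aims); two-sided alpha 0.05, power 0.95, d = 2.76 and d = 1.38, 15 per group (Power calculation). The document gives no correlations between outcomes or visits, so those below are assumptions.

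**Step 1: reproduce the plan's sample sizes.** I used exact two-sample t-test power from the noncentral t distribution, with 2n − 2 degrees of freedom and noncentrality d·√(n/2), at two-sided 0.05.
- d = 2.76: n = 5 per group gives power 0.967. The plan states 5.
- d = 1.38: n = 14 gives 0.940 and n = 15 gives 0.954. The plan states 15.

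Both figures reproduce. A one-sided test would give 4 and 13, which do not match. The 0.05 is therefore the level of one two-sided t test, with no allowance for several outcomes.

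**Step 2: any of the four outcomes at 3-month follow-up may count.** Assume WBT has no effect on any outcome and each test is at 0.05.
- At least one false positive, independent tests: 1 − 0.95⁴ = 0.185.
- At least one false result in favour of WBT, independent tests: 1 − 0.975⁴ = 0.096, against 0.025 for one test.
- With positive correlation, from 40,000 simulated trials per setting (15 per arm, unadjusted two-sided t tests), the chance of at least one false positive in either direction is:

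| Assumed correlation between outcomes | At least one false positive |
|---|---|
| 0.3 | 17.2% |
| 0.5 | 15.5% |
| 0.7 | 13.4% |
| 0.9 | 9.5% |

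The plan names ANCOVA and the simulation uses t tests. Each single comparison has a 5% level under either method, so only the correlation between comparisons could differ.

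**Step 3: the outer cases.**
- All 4 × 3 = 12 outcome-by-visit tests may count and are independent: 1 − 0.95¹² = 0.460. With assumed correlations of 0.3 to 0.9 between outcomes and 0.5 to 0.9 between visits, the simulated figure falls from 39.5% to 15.6%.
- All four outcomes must differ: the false-positive chance is at or below 0.05, and power is lower than for a single test.

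**Step 4: what naming one comparison costs.** At the plan's own disability effect, d = 2.76, 15 per group gives power above 0.99 at two-sided 0.05. Bonferroni over 4 tests (0.05/4 = 0.0125) or 12 tests (0.05/12 = 0.0042) would need 7 or 8 per group at that effect for 0.95 power, so 15 would still be enough.

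**The case against.** The strongest reply is that this is a pilot. The Data analysis plan puts description first, Study overview speaks of preliminary effects, and the Discussion calls the trial exploratory. The 0.05 appears only as an input to the sample size. No section promises family-wise control or makes a p-value below 0.05 the criterion for success. This stands: no stated guarantee is broken.

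Three stronger readings are tempting, and the documents do not support them.
- A reader might infer a 46% false-positive rate. That needs all 12 tests to count and to be independent. Aim 1 runs to the 3-month follow-up, which points to that visit, and the analysis section does not say that 12 separate tests will be run. The 46% is an upper case only.
- A reader might infer that any single difference is enough. The hypothesis is worded for the four outcomes together, so a rule that all must improve is equally open and would not inflate the error. The text supports neither rule over the other.
- A reader might take the power at d = 1.38 as the primary outcome's power, and so conclude that adjusting for multiplicity costs a good deal. That effect belongs to the secondary Psychological Well-being scale. At the disability effect the plan assumes, the adjustment is affordable.

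It is also fair to say that a false pilot signal would still have to pass the second trial, and that methods of adjustment may sit in an analysis plan not shown. Neither point identifies the deciding outcome. The protocol itself states a directional primary hypothesis, sizes for 0.95 power and ties the next trial to support for that hypothesis. A purely descriptive pilot would need none of these.

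**Conclusion.** The point holds as a problem of an unspecified deciding comparison. The 0.05 describes the test of the primary hypothesis only if one comparison decides it, and none is named.

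If any of the four outcomes at 3-month follow-up may count, the chance of at least one false positive is about two to nearly four times the single-test level (9.5/5 = 1.9; 18.5/5 = 3.7). This rests on three assumptions: no true effect on any outcome, unadjusted tests at 0.05, and the assumed correlations. Under an all-must-differ rule there is no inflation. The consequence lies in how the pilot's result can be interpreted and used to justify the next trial. The change should be made, and it is easy to make now because Trial status says recruitment has not begun.

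**What to change.** Before recruitment, name one deciding comparison in Specific aims and Primary outcomes. An example is the between-arm ANCOVA difference in the Migraine Disability Assessment score at 3-month follow-up. It is the only primary measure used in Power calculation. The 3-month visit also suits its recall period of 3 months: with sessions every other week, session 4 falls about 6 weeks after session 1 (3 × 2), so a score taken then would reach back before therapy began. Attack frequency, duration and intensity, and all session 4 and session 8 results, would be reported as supportive with estimates and 95% intervals. The Discussion should say that only the named comparison counts as support for the hypothesis.

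An acceptable alternative, closer to the stated descriptive emphasis, is to declare all clinical comparisons descriptive with intervals. The Discussion would then no longer rest the next trial on support for a tested hypothesis.

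Either route changes wording only: sample size, visits and instruments stay as they are. With the first route, the remaining outcomes and visits can no longer be claimed as confirmation. With the second, none can.

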### Secondary outcomes

Secondary outcomes focus on anxiety, depression, psychological well-being, euthymia, and distress. These variables are assessed at baseline (prior to randomization), at the end of session 4 and 8 of the treatment, and at 3-month follow-up. Anxiety and depression will be assessed via the Symptom Questionnaire [42, 43], a self-administered 92-item dichotomous scale (yes/no or true/false), of which 68 items indicate symptoms (symptom subscales) and 24 items are antonyms of some of the symptoms and indicate well-being (well-being subscale). Higher subscale scores indicate higher severity of symptoms or higher well-being, respectively. The Symptom Questionnaire had good validity and reliability [43]. Psychological well-being will be assessed via (1) the World Health Organization-Five Well-Being Index [44], a self-administered 5-item scale, with answers rated on a 6-point Likert scale assessing well-being in the 2 previous weeks, wherein the higher the score, the higher the level of well-being; and (2) the Psychological Well-Being Questionnaire [45], a 84-item self-administered inventory, rated on a 6-point Likert scale, measuring six constructs, namely Autonomy (i.e., independence and self-determination); Environmental Mastery (i.e., ability to manage one’s life); Personal Growth (i.e., being open to new experiences); Positive Relations with others (i.e., having satisfying relationships); Purpose in Life (i.e., believing that one’s life is meaningful); and Self-Acceptance (i.e., having a positive attitude towards oneself and past life). The Psychological Well-Being Questionnaire has shown good psychometric properties [46].

Euthymia will be assessed via the Euthymia scale [47], a self-administered scale consisting of 10 items with a dichotomous response mode (yes/no or true/false). The higher the score, the higher the level of euthymia [47]. Distress will be measured via the Psychosocial Index [48], a 55-item questionnaire assessing stress, wellness, illness behavior, psychological distress, and quality of life; it showed good psychometric properties [49]. Some questions of the Psychosocial Index require specific responses, most of them provide a dichotomous response, others are measured on a 4-point Likert scale. The final item, on the quality of life, has five possible answers.

### Assessment training

All IEs are Ph.D.-level researchers with extensive prior diagnostic assessment experience. Regardless of familiarity with study assessment measures, all IEs will receive additional training on the primary and secondary clinical outcome measures prior to conducting study assessments. This includes training on viewing and rating clinical outcome measures, created by the principal investigator (FC). RAs will follow our standard training protocol under the direction of the study investigators. This structured training protocol consists of a graduated set of tasks and experiences, beginning with reading relevant papers, studying instruments and instruction booklets, multi-day didactics, and reviewing suggestions for handling common interviewing problems. RAs are closely supervised during these training sessions and during their initial interviews by the principal investigator (FC).

### Data management and statistical analysis plan

#### Data collection, management and assurance of quality

Data from the self-report questionnaires, self-report headache diary, and the MINI will be first recorded on paper forms and then entered into the SPSS 20.0 (Statistical Package for Social Science) [50] macro and verified by research staff. Several data monitoring procedures will be implemented to ensure data quality, including (1) systematically recording study notes-to-file in the case of any event that threatens data integrity and (2) routine internal audits confirming proper informed consent, accurate completion of data forms, and documentation of missing data.

#### Data analysis plan

We will primarily focus on descriptive statistics to examine both feasibility, acceptability, and outcomes. This includes examining rates of study recruitment, participant’s willingness to be randomized, session attendance, and patient satisfaction. Additionally, we will compare rates of migraine attacks per month and their duration as well as the level of disability due to migraine and psychological measures. We will also examine the means of key variables (i.e., level of pain and disability caused by migraine, frequency, duration, and intensity of migraine attacks, anxiety, depression, psychological well-being, euthymia, distress) across baseline, session 4, session 8, and 3-month follow-up. We will use ANCOVA to compare means of variables [51], χ^2^ to compare frequencies, and a multivariate logistic regression analyses to identify independent predictors of psychological well-being among socio-demographic and psychological variables measured at baseline. The number of migraine attacks are recorded via the headache self-report daily diary following the rules suggested by Tfelt-Hansen et al. [36], namely (1) a migraine attack which is interrupted by sleep, or temporarily remits, and then recurs within 48 h is recorded as one attack; (2) an attack treated successfully with medication but with relapse within 48 h counts as one attack; and (3) a practical solution to differing these using diary entries over the previous month is to count as distinct attacks only those that are separated by an entire day headache free.

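### The predictor analysis names a logistic model for well-being scores that are graded and have no stated binary definition, and 30 patients cannot support an open search for independent predictors

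*Protocol article*

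**What the plan says.** The Data analysis plan section of the protocol article lists, after ANCOVA for means and chi-squared tests for frequencies, "a multivariate logistic regression analyses to identify independent predictors of psychological well-being among socio-demographic and psychological variables measured at baseline".

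The Secondary outcomes section measures psychological well-being with two instruments. One is the WHO five-item index, scored so that it is graded throughout ("wherein the higher the score, the higher the level of well-being"). The other is the Psychological Well-Being Questionnaire, "a 84-item self-administered inventory, rated on a 6-point Likert scale, measuring six constructs". The article gives no threshold, responder rule or other binary version of either.

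The Data analysis plan itself treats the variable as continuous elsewhere: "We will also examine the means of key variables", and psychological well-being is on the list that follows.

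The Power calculation section fixes the size: "Thus, we will enroll 15 subjects per group for a total of 30 subjects". Drop-outs are to be replaced so that 15 per group complete. The Discussion concedes that "the sample size will not allow to test for potential differences in outcome between different durations of the chronic migraine", and says the same of levels of severity.

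**The concern.** There are two separate problems.

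1. **Model and outcome do not match.** Ordinary logistic regression needs a two-category outcome. The article measures well-being only on graded scales and elsewhere analyses its means. To fit the stated model, someone must cut the score at a point the article does not give, and the cut discards the differences between patients on the same side of it.

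2. **The sample does not suit the goal.** The stated goal is to identify independent predictors, which is an inferential task. The trial was sized only for a two-group t test. A multivariable search over baseline variables asks more of the same 30 patients than the subgroup comparisons that the Discussion already rules out.

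At stake are lost power for any real predictor, unstable odds ratios, and a fair chance that a predictor reported from this pilot is noise.

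**Working it through.** **Step 1: the plan's own sample size.** Inputs, from Power calculation: "Setting the power at 0.95 and the two-sided alpha at 0.05", with Cohen's d = 1.38 (well-being scale) and 2.76 (disability scale). The normal approximation is n per group = 2(1.960 + 1.645)² / d².
- d = 1.38: 2 × 12.996 / 1.904 = 13.65, so 14. The exact t calculation gives 14.68, so 15, with power 95.4% at 15.
- d = 2.76: 2 × 12.996 / 7.618 = 3.41, so 4. The exact t calculation gives 4.64, so 5, with power 96.7% at 5.

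The stated 15 and 5 per group reproduce. They concern a comparison of two means, not a predictor model.

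**Step 2: events per candidate.** The cut-point is assumed to be the median, which gives the largest possible smaller category: 30 / 2 = 15. The number of candidates k is not given, so a range is shown. The article names about eight that fit the description: age, sex and education (Randomization), and anxiety, depression, well-being, euthymia and distress (Secondary outcomes).
- k = 3: 15 / 3 = 5.0 per candidate
- k = 8: 15 / 8 = 1.9
- k = 12: 15 / 12 = 1.25

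An uneven cut gives fewer.

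**Step 3: information lost by the split.** For a normal outcome and a weak effect, a median split keeps 2/π = 0.637 of the information. The loss is about 36%, as if 30 × 0.637 = 19 patients had been used.

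**Step 4: power for one true predictor.** Simulation, n = 30, median split, correlation 0.5 between predictor and score:

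| Analysis | Power |
|---|---|
| Linear, continuous score | about 84% |
| Logistic, likelihood-ratio test | about 66% |
| Logistic, Wald test | about 56% |

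Repeat runs gave 82–84%, 64–66% and 53–57%. By likelihood ratio, the loss at other correlations is from 61% to 45% (correlation 0.4) and from 95% to 83% (correlation 0.6). With eight predictors in the model and one of them true at 0.5, power is about 70% linear, 57% by likelihood ratio and 37% by Wald.

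**Step 5: chance predictors under no association.** For k independent tests at 0.05, the chance of at least one p < 0.05 is 1 − 0.95^k: 14% for k = 3 and 34% for k = 8. Simulated full models with independent candidates:

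| Candidates | Logistic | Linear |
|---|---|---|
| 3 | 12% | 15% |
| 5 | 20% | 19% |
| 8 | 29–30% | 28% |

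With candidates correlated at 0.4 the rates are 9% and 11% for three, and 28% and 29% for eight. If the best single candidate is selected by likelihood ratio, the rate for eight is 34–40%.

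**Step 6: failure of the logistic fit.** Separation or failure occurs in about 1–2% of runs with 8 candidates and about 22% with 12. With 3 it did not occur.

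**The case against.** The strongest defence is that this is a side analysis in a small pilot. The Data analysis plan puts descriptive statistics first, the Discussion calls the trial exploratory, and the Specific aims do not mention predictors. The cut-off, the candidate list and the selection rule are details that an article may leave to a fuller document. With three candidates the risks are modest. An ordinal logistic model would also lose less information than a split, although the article does not mention one.

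Most of this stands, and it limits the weight of the point. It does not remove it. A fuller document could add a cut-off or shorten the list, but splitting a graded score would still lose information, and 30 patients would still be too few for an open search.

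A reader might also infer four stronger things that the article does not support:

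- **That the logistic choice causes the chance predictors.** It does not. Step 5 shows nearly the same rate under a linear model. The causes are the small sample and the open list.
- **That a false predictor will probably be reported.** With eight null candidates, most full models show none.
- **That treatment arm is left out of the model.** The sentence describes where predictors are sought. It does not show that arm is excluded.
- **That the result will steer patient selection in the next trial.** The Discussion ties the next trial to support for the study hypothesis, not to this model.

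The power figures depend on the test. The Wald test is the least favourable reading, and the likelihood-ratio test is somewhat liberal at this size, so a fair figure lies between the two. Both fall well short of the linear model.

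**Conclusion.** The point holds, at minor severity. The article names a binary-outcome model for a variable that it measures only on graded scales and elsewhere analyses by its means. At a correlation of 0.5 and n = 30, the cost is about 18 percentage points of power by likelihood ratio (84 − 66) or 28 by Wald (84 − 56). Separately, whichever model is used, the search is prone to report chance predictors: about 12–15% of full models with three candidates and 28–30% with eight.

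These figures assume a median split, normally distributed scores, independent candidates and 30 completers. The number of candidates is also assumed. The mismatch between model and outcome rests on none of these; it is in the text. Neither the treatment comparison nor the sample-size figures are affected.

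**What to change.** Either delete the logistic model, or replace it with linear regression on the continuous well-being score at follow-up, adjusted for baseline score and arm, with one or two predictors named in advance. Report the estimates with 95% confidence intervals, label them exploratory, and do not select by p value. Both parts are needed: the continuous score recovers the lost information, but only the short list named in advance limits chance findings.

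The cost is the wording of one sentence, and the Trial status section says recruitment has not started. The downside is that fewer predictors are examined.
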